## Abstract

**Background:**

Management of benign vocal fold lesions (BVFLs) is variable with individuals receiving surgery, voice therapy, or a combination of these approaches. Some evidence suggests that the best outcomes may be achieved when patients are offered pre- and post-operative voice therapy in addition to phonosurgery, but what constitutes pre- and post-operative voice therapy is poorly described. The pre- and post-operative voice therapy (PAPOV) intervention has been developed and described according to the TIDieR checklist and Rehabilitation Treatment Specification System (RTSS) for voice. The PAPOV intervention is delivered by specialist speech and language therapists trained in the intervention and comprises 7 essential and 4 additional components, delivered in voice therapy sessions with patients who are having surgery on their vocal folds for removal of BVFLs.

**Study design:**

Non-randomised, multicentre feasibility trial with embedded process evaluation.

**Method:**

Forty patients from two sites who are due to undergo phonosurgery will be recruited to receive the PAPOV intervention. Measures of feasibility, including recruitment, retention, and adherence, will be assessed. The feasibility of gathering clinical and cost effectiveness data will be measured pre-treatment, then at 3 and 6 months post-operatively. An embedded process evaluation will be undertaken to explain feasibility findings.

**Discussion:**

This study will assess the feasibility of delivering a described voice therapy intervention protocol to patients who are undergoing surgery for removal of BVFLs. Findings will be used to inform the development and implementation of a subsequent effectiveness trial, should this be feasible.

**Trial registration:**

This trial has been prospectively registered on ISRCTN (date 4th January 2023), registration number 17438192, and can be viewed here: https://www.isrctn.com/ISRCTN17438192.

## Background

Voice is a vital part of everyday human communication; however, one in three people will experience dysphonia in their lifetime [1]. The aetiology of dysphonia can be multifactorial, including muscle tension, tissue inflammation, nerve damage, or structural changes on the vocal folds [2]. Vocal fold cysts, polyps, papilloma, and Reinke’s oedema are examples of structural changes, termed ‘benign vocal fold lesions’ (BVFLs). BVFLs cause dysphonia by causing irregular vibration, preventing vocal fold closure, and increasing compensatory muscle tension [3, 4].

Voice loss because of BVFLs impacts individuals, society, and health resources. Individuals struggle to communicate on a daily basis and are unable to partake in hobbies, socialise, or fulfil caring responsibilities. Reduced activity and participation in society leads to increased rates of social isolation, anxiety, and depression [5, 6]. It is estimated that consequential time off work alone costs the UK £200 million each year [7] and direct healthcare costs in the US total £10–11 billion per year, making dysphonia comparable with COPD and diabetes [8, 9].

There are no clinical guidelines determining management for patients with BVFLs [10]. Patients may be offered surgery, pharmacological management, voice therapy, or a combination of approaches [11]. Pre-operative voice therapy can result in avoidance of surgery in up to 50% of patients with vocal fold polyps [10, 12–14]. Voice therapy may lead to lesion regression due to a reduction of phonotraumatic behaviours, improvement of throat symptoms as a result of improved voice care, or a reduction of muscle tension patterns. Emerging research suggests that voice therapy delivered by a specialist speech and language therapist (SLT) pre- and post-operatively gives greater improvement than surgery alone [15, 16]. However, it is unclear which elements of voice therapy are most effective, when they should be introduced or with which patients. In addition, treatment for individuals with BVFLs is influenced internationally by local capacity, historical practice, and surgeon preference [11, 17]. This can result in sub-optimal patient care [18], unnecessary surgery, additional hospital appointments, prolongation of symptoms [19], secondary complications from surgery [20], raised anxiety, and financial consequences [8].

Voice therapy is a complex intervention comprising multiple, interacting components [21]. To assess the effectiveness of a complex intervention, work must first be undertaken to interrogate the active ingredients in the intervention, the context in which it is delivered and the flexibility or tailoring which occurs in clinical practice. The Rehabilitation Treatment Specification System (RTSS) for voice [22] has proposed unique and specific targets and ingredients for voice therapy. The aim of this is to improve descriptions of voice therapy interventions and untangle the ‘black box’ scenario around complex interventions. Currently it can be unclear what is meant by generic treatment descriptions. The Medical Research Council’s framework for developing and evaluating complex interventions [23] advocates a structured developmental pathway by undertaking preliminary intervention development work, followed by feasibility testing. This reduces the likelihood of research waste, which they describe is an inevitable consequence of failing to devote adequate time to developing, describing, and testing a complex intervention [21, 24]. Work has now been completed to identify the potential ingredients in a best practice voice therapy intervention. This has involved the triangulation [25] of findings from a systematic review [26], expert interview study [17], national survey of current practice [27], a Delphi consensus study [28], and extensive Patient and Public Involvement and Engagement (PPIE) activities.

The outcome is a Pre- And Post-Operative Voice therapy intervention (PAPOV) which is described in detail, in accordance with the TIDieR checklist [29], and according to the Rehabilitation Treatment Specification System (RTSS) for voice [22, 30]. The PAPOV intervention has been specifically developed for adults who are undergoing phonosurgery to have BVFL(s) removed. It is hoped that patients who receive the PAPOV intervention will feel prepared for their surgery, understand how to optimise their preparation for and recovery from surgery, and develop the vocal skill necessary for long-term healthy voice management. It is now appropriate to test the feasibility of delivering this intervention to patients who are undergoing phonosurgery for removal of BVFLs.

This research will address key uncertainties in undertaking a trial of pre- and post-operative voice therapy, such as recruitment, retention, intervention fidelity, and acceptability.

## Aims and objectives

This paper describes a non-randomised multicentre feasibility trial with an embedded process evaluation. The aim of the trial is to explore feasibility elements including recruitment, retention, delivery of the voice therapy intervention, completion of clinical outcomes, and economic evaluation data. An embedded process evaluation will investigate the delivery, context, and mechanisms of impact in the PAPOV intervention, in order to explain feasibility findings.

Primary feasibility objective: The primary objective is to measure the feasibility of delivering the PAPOV intervention in a multicentre, non-randomised trial to patients undergoing phonosurgery for benign vocal fold lesions.

The feasibility trial objectives are to gather data regarding the following parameters:Number of eligible patients, measured using the eligibility log and surgical lists at each site at the end of the studyNumber of patients recruited and consented to the trial, as a proportion of those eligible, measured using the eligibility log at each site at the end of the studyNumber of patients completing the study, as a proportion of those recruited measured using the case report form at the end of the studyThe amount of clinical outcomes data completed, measured using the case report form at each time point (baseline, 3 and 6 months post-surgery) (%)The amount of health economics data completed, measured using the case report form at each time point (baseline, 3 and 6 months post-surgery) (%)

Process evaluation objectives are:Number of voice therapy sessions received by each patient measured using clinical notes at the end of the studyLevel of adherence to the PAPOV intervention within voice therapy sessions measured as the number of essential components documented in clinical notes for each sessionDescription of any adaptations or alterations made to the PAPOV intervention measured using analysis of clinical notes for each session and analysis of clinician interviewsThe amount and completeness of home practice measured using adherence questionnaire data completed by participants at the end of their voice therapy sessionsDescription of participating sites and participants, measured using the case report form at the end of the studyUnderstand clinicians’ experiences of being trained to deliver the intervention and trial processes, measured using an analysis of clinician mentoring records and interview data with clinicians at the end of the studyUnderstand clinicians’ experiences of delivering the intervention including acceptability, barriers, and facilitators measured using analysis of clinician mentoring records and interview data with clinicians at the end of the studyUnderstand participants’ experiences of trial processes measured using analysis of interview data at 6 months post-surgeryUnderstand participants’ experiences of receiving the PAPOV intervention including acceptability, barriers, and facilitators measured using analysis of interview data at 6 months

## Methods

### Study design

This is a multicentre, non-randomised, feasibility trial with an embedded process evaluation.

Problems associated with acceptability, compliance, delivery of the intervention, recruitment, retention, and effect sizes can occur if preparatory work is insufficient when evaluating the effectiveness in a definitive RCT [24]. The mixed methods design permits the depth of data collection and analysis required to inform changes in a definitive trial. The multicentre design will permit additional feasibility parameters to be gathered. This protocol follows guidance in the ‘CONSORT 2010 statement: Extension to randomised pilot and feasibility trials’ [31]. Process evaluation is an essential part of designing and testing complex interventions. Investigating the implementation of the intervention, including the fidelity, dose, adaptations, and reach, along with the context and mechanisms of impact informs interpretations of the outcomes of the trial. The Medical Research Council recommends including process evaluation at the feasibility stage, to understand and interpret feasibility findings and inform further development and evaluation stages [23, 32].

### Participants

Patients with BVFLs who have been consented for phonosurgery by an Ear Nose and Throat (ENT) surgeon as part of their management will be eligible for enrolment. Table 1 lists the inclusion and exclusion criteria. Fig. 1 shows a flow diagram detailing eligibility and screening procedures.

**Table 1 Tab1:** Inclusion and exclusion criteria

Inclusion criteria
• ≥ 18 years of age
• Willing and able to offer informed consent to the study
• Presence of unilateral or bilateral benign vocal fold lesion on the vibrating portion of the vocal fold (including one or a combination of these diagnostic categories: fibrotic vocal fold nodules, polyp, cyst, pseudocyst, polypoid fringe, sulcus, mucosal bridge, papilloma)
• Clinical diagnosis confirmed using video laryngostroboscopy
• ± presence of additional muscle tension dysphonia/inflammation
Exclusion criteria
• Diagnosis of soft vocal fold nodules; these patients receive a different pathway of care and surgery would not be offered as first line treatment
• Diagnosis of arytenoid granuloma; this does not affect the vibratory portion of the vocal fold
• Previous phonosurgery due to the potential for scarring
• Suspicion of malignancy requiring urgent microlaryngoscopy and biopsy; principles of phonosurgery for malignancy are different from benign lesions

**Fig. 1 Fig1:**
[figure not shown]
Eligibility and screening flow diagram

### Sampling

We aim to recruit 40 participants from 2 sites, aiming for between 15 and 25 per site. Additionally, clinicians delivering the intervention will be invited to take part in interviews (*n* = 4–6).

Sample sizes of between 24 and 50 participants are recommended to give sufficient information to estimate key parameters in feasibility trials [33, 34]. This trial aims to recruit 40 participants over 2 sites. Audit data from Nottingham confirms surgical data of over 70 eligible patients per annum with other centres reporting comparable figures, meaning it will take an estimated 7 months to recruit 20 patients if a conservative recruitment rate of 50% is achieved [35]. Regardless of the number of enrolled participants, recruitment will stop after 10 months on each site, owing to the timescales for the project. Data from a systematic review of functional voice therapy reported attrition rates of 0–39% meaning that as a minimum, > 24 participants are expected to complete the intervention.

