### Primary feasibility outcomes

Recruitment: The number of patients recruited to the trial as a proportion of those eligible will be measured at each site. Audit data from site one confirmed surgical data of over 70 eligible patients per annum, meaning it will take 7 months to recruit 20 participants per site, if a conservative recruitment rate of 50% is achieved. Recruitment figures will be monitored on a monthly basis at the trial management group and a decision to open a third site will be triggered if recruitment falls below 50% of the target after 4 months.

Retention: The number of patients completing the study as a proportion of those recruited will be measured. Data from a systematic review of functional voice therapy reported attrition rates of 0–39%. Attrition rates will therefore be considered acceptable if they remain below 39%. Reasons for attrition will be considered. These will specifically be explored from both the clinician perspective and the participant perspective using semi-structured interviews.

Data completion: The amount (%) of clinical and health economics data completed will be measured at each timepoint (Baseline, 3 and 6 months post-surgery). Data checks will be undertaken throughout to identify if there is missing data and the reasons for this. Steps to address this will be implemented as required during the trial, such as the provision of additional technological support, participant reminders, offering face to face appointments for data completion.

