### Trial progression

The trial will be deemed successful based on the following:Recruitment: Recruitment of > 50% of eligible participants into the trialRetention: Participant attrition below 39%, based on the number of participants completing the trial as a proportion of those consented

Modifications should be made to a future trial design if feasibility outcomes fall below the above criteria. Analysis of intervention fidelity data, participant and clinician interviews will inform the need for any modifications to the intervention in a subsequent trial.

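### The success rule is two ratios with no count or rate, so a trial that closes at 10 months well short of its aim of 40 can still be deemed successful

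*Protocol article*

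**What the plan says.** The Sampling section argues from numbers. The aim is "We aim to recruit 40 participants from 2 sites, aiming for between 15 and 25 per site". The supporting statement is "Sample sizes of between 24 and 50 participants are recommended to give sufficient information to estimate key parameters in feasibility trials". The forecast starts from "Audit data from Nottingham confirms surgical data of over 70 eligible patients per annum with other centres reporting comparable figures" and concludes that "it will take an estimated 7 months to recruit 20 patients if a conservative recruitment rate of 50% is achieved". On losses, a systematic review "reported attrition rates of 0–39% meaning that as a minimum, > 24 participants are expected to complete the intervention". The same section fixes the end of recruitment by calendar: "Regardless of the number of enrolled participants, recruitment will stop after 10 months on each site, owing to the timescales for the project".

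The Trial progression section names two conditions for success. One is enrolment of more than half of the eligible patients. The other is "Participant attrition below 39%, based on the number of participants completing the trial as a proportion of those consented". If outcomes fall short of these, a future trial design should be modified. Neither condition carries a number of participants or a rate per month.

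The count appears elsewhere only as an in-trial measure. Under Primary feasibility outcomes, "a decision to open a third site will be triggered if recruitment falls below 50% of the target after 4 months". The termination section lets the sponsor and funder stop the study for poor recruitment at their discretion.

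**The concern.** A ratio of recruited to eligible says how willing patients are. It does not say how many there are. The number of eligible patients is the first feasibility objective listed, yet no value of it can change the verdict. If eligible flow is much lower than the audit suggested, uptake can still exceed 50%, recruitment still closes at 10 months, and the trial is deemed successful with a sample well below the one used to justify it.

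Two things are at stake. Planning a definitive trial needs recruits per site per month as well as uptake. The Analysis plan also intends to use change from baseline to 6 months to inform the next sample size, and the precision of that depends on how many people are followed up.

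**Working it through.** **Inputs from the protocol article.** Eligible flow 70 per site per year (stated as over 70); uptake 50%; two sites; 10-month window per site; aim 40, 15 to 25 per site; recommended size 24 to 50; attrition limit 39%. Flows below 70 are assumptions, shown as a range.

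**The plan's own figures reproduce.**
- Eligible per site per month: 70/12 = 5.83. Recruits at 50%: 2.92.
- Months to recruit 20: 20/2.92 = 6.9, against 7 stated.
- Completers from 40 at 39% attrition: 40 × 0.61 = 24.4, against more than 24 stated.
- Two sites over 10 months: 20 × 5.83 = 117 eligible and about 58 recruits at 50%, so the aim is met with room to spare.

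**Where 50% uptake stops delivering the numbers.** Two sites for 10 months give 20 site-months.
- 40 recruits need 80 eligible: 80/20 = 4 per site per month, or 48 per site per year.
- 24 recruits need 48 eligible: 48/20 = 2.4 per site per month, or 28.8 per site per year.

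**Smallest counts that still pass both ratios** (eligible rounded down; recruits just above 50%; the most losses that stay below 39%):

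| Eligible per site per year | Eligible, 2 sites, 10 months | Recruited | Lost | Completers |
|---|---|---|---|---|
| 70 | 116 | 59 | 23 (39.0%, just under the limit) | 36 |
| 48 | 80 | 41 | 15 (36.6%) | 26 |
| 40 | 66 | 34 | 13 (38.2%) | 21 |
| 30 | 50 | 26 | 10 (38.5%) | 16 |
| 20 | 33 | 17 | 6 (35.3%) | 11 |
| 15 | 25 | 13 | 5 (38.5%) | 8 |

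**What this does to precision.** Wilson 95% interval for attrition: 15 of 40 lost, 24% to 53%; 6 of 17 lost, 17% to 59%. For a standard deviation, the 95% limits as multiples of the estimate are √[(n−1)/χ²] at the upper and lower 2.5% points: 0.78 to 1.39 with 25 completers and 0.66 to 2.04 with 8. A sample size scales with the square, so the factor runs from 0.61 to 1.9 with 25 and from 0.44 to 4.1 with 8.

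**Whether the third-site trigger would act.** The section does not define the target. Pro rata at month 4, half the target is 40 × (4/10)/2 = 8 on a 10-month schedule, or 40 × (4/7)/2 = 11.4 on a 7-month schedule. At even accrual, month-4 recruits are four tenths of the 10-month total:
- 34 recruits: 13.6, no trigger on either schedule.
- 26 recruits: 10.4, trigger on the 7-month schedule only.
- 17 recruits: 6.8, trigger on both.
- 13 recruits: 5.2, trigger on both.

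**The case against.** The strongest reply is that the shortfall is conditional and partly guarded against. The audit figure would have to be well off before 40 is missed. Patients already on the waiting list are invited too, which adds a stock to the annual flow. The third-site trigger would probably act in the worst cases, and the sponsor and funder can stop the study. All of this stands and makes the extreme rows of the table unlikely. But these measures guarantee no number, and none of them enters the success rule. The trigger may also stay silent for moderate shortfalls, as the 34-recruit row shows.

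Three stronger readings are tempting but not supported.
- A reader might infer that the plan breaches a required minimum. The Sampling section speaks of an aim, a recommendation and an expectation. It sets no minimum, and a trial that recruits 24 lies inside the cited range.
- A reader might infer that the third-site rule contradicts the success rule, since one could call recruitment poor and the other call it a success. The first is an operational trigger during the trial and the second an end-of-study judgement. Both sections define the recruitment outcome as a proportion of those eligible. They can differ without contradiction.
- A reader might infer that the remedy is a floor of 24 completers. That would fail a trial with 37 recruits and 14 lost (37.8%, 23 complete), where accrual is close to the aim. At 30 recruits, the bottom of the 15 to 25 per site range, it would cut permitted attrition to 6/30 = 20%. The plan's figure of more than 24 also refers to completing the intervention, not to 6-month follow-up.

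It is also fair that low flow would be visible in the report, because eligible numbers are to be collected. The gap is only that they do not count towards the verdict.

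**Conclusion.** The point holds as a gap in the success rule. The plan's arithmetic is correct. Followed exactly, however, the rule can return success after the trial has missed the numbers that justify it. This needs an eligible flow below about 48 per site per year to miss 40 recruits, or below about 29 to miss 24, with two sites, uptake at about 50% and the full 10-month window. Higher uptake or a third site moves these thresholds down. The lower flows are assumptions; the document gives no evidence that they will occur. With fewer completers the key parameters would be estimated less precisely; it would be too strong to say that they could not be estimated.

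**What to change.** In the Trial progression section, add a count or rate to the recruitment criterion, taken from the Sampling section. For example: at least 15 recruits per site within the 10-month window (15/10 = 1.5 per site per month; 30 over two sites), otherwise the conclusion is that the design needs modification. Expressed as a rate per month open, it also covers a third site that opens late. Keep the attrition criterion as a proportion.

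Report eligible patients and recruits per site per month beside the forecast of about 5.8 and 2.9.

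At 50% uptake this floor is reached when flow is 36 eligible per site per year (15/0.5 = 30 in 10 months). It does not secure more than 24 completers: 30 recruits with 11 lost (36.7%) leaves 19. It catches a failure of accrual and leaves retention to its own criterion.

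The cost is a sentence or two and no new data. The small downside is one more way to reach the conclusion that modification is needed.
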